**Methods:**

The study is designed as a multi-centric two-arm randomized clinical trial including an intervention group and a placebo control group, allocation concealment, single-blinding, and intention-to-treat analysis. Participants (*N* = 334) will be continuously recruited from four clinics specialized in the treatment of MDD. The intervention builds on a standardized, theory-based, low-cost lifestyle physical activity counselling programme, which was specifically designed for an in-patient rehabilitation setting. The placebo control condition consists of general instructions about health-enhancing physical activity. Data assessments will take place 2–3 weeks after admission to in-patient treatment (baseline), and 6 weeks (post) and 12 months (follow-up) after discharge from in-patient treatment. The primary outcome is objectively assessed physical activity at follow-up.

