### Physical activity counselling and behavioural skill training to foster regular exercise participation

Several theories have been developed to facilitate change in health behaviour [78]. Two recent models are the Health Action Process Approach model [79] and the Motivation and Volition-process model [80]. The common ground of these models is that they focus on both motivational (how people form an intention) and post-intentional (volitional) processes, including action planning, identification of personal and environmental barriers, coping planning, and relapse management. Both models have resulted in theory-based intervention programmes that provide support for long-term behaviour change in overweight people and patients suffering from somatic conditions [81–84]. As an example, Fuchs et al. [81] showed that amongst 220 inactive in-patients of an orthopaedic rehabilitation clinic, motivational and volitional counselling resulted in a moderate-to-large short-term increase (*d* = 0.72) in physical activity in the intervention group compared to the control group. Although the group difference diminished until 12-month follow-up, the intervention group still reported increased physical activity levels. Nevertheless, while these findings are promising, research about the potential of such programmes in patients with MDD is scarce.

A recent study showed that lifestyle counselling (including diet, exercise, sunlight exposure, and sleep) can be an effective add-on to antidepressant treatment. While remission reached 60% in the combined treatment group, this rate was considerably lower in the control group (10%) [85]. So far, only one RCT exists in which the effects of individually tailored physical activity counselling through professionally trained physical activity facilitators have been tested in patients with MDD [86–88]. While the findings showed that the intervention group had significantly increased physical activity levels at follow-up, this study was carried out in an out-patient setting, did not focus on patients with low physical activity levels, and did not assess physical activity objectively.

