## Methods/design

### Study design

The study is designed as a multi-centric, two-arm RCT including an intervention group (IG) and a placebo control group (PCG), allocation concealment, single-blinding, and intention-to-treat analysis. The study is a cooperation between four Swiss psychiatric clinics (two public, two private) and the Department of Sport, Exercise and Health of the University of Basel. Figure 1 provides an overview of the planned study design. The 25-item CONSORT checklist was used when designing the study. Figure 2 represents the SPIRIT figure, providing an overview of foreseen time points, interventions, and assessments. The description of the study protocol contains all elements listed in the SPIRIT checklist (see Additional file 1).

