#### Intervention programme: individually tailored physical activity promotion

Patients assigned to the IG will receive an individually tailored physical activity counselling to provide support and encouragement to increase physical activity. Two face-to-face meetings will take place during the clinical treatment which lasts between 6 and 8 weeks on average. The meetings will take place approximately in weeks 4 and 6 of in-patient treatment. The same physical activity facilitator will develop a physical activity plan with the participant, tailored to the individual’s current activity levels, activity type, and intensity preferences, and will promote behavioural change techniques which have been proven effective in previous studies [102–107]. Additionally, starting 1 week after discharge from in-patient treatment, patients of the IG will receive bi-weekly telephone counselling and SMS prompts until 12 months after discharge. Telephone counselling and push notifications will help to ensure adherence of patients to their physical activity and exercise plans/prescription, or facilitate the adaptation of these plans. Furthermore, a smartphone app will be developed which can be used to support patients in their planning and self-monitoring of physical activity and exercise behaviour.

Exercise prescriptions follow the standards of the American College of Sports Medicine [90, 91], stating that individuals should engage in at least 30 min of moderate-intensity physical activity on 5 days per week, or 20 min of vigorous-intensity aerobic exercise on 3 days each week. A variety of activities such as aerobic exercise, resistance exercise, multi-modal group-based exercise, daily physical activity (e.g. walk or take bike for grocery shopping), and so forth, will be advised.

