### Primary outcome

#### Objective physical activity

Objective physical activity will be assessed with an accelerometer (wGT3x-BT; Actigraph, Shalimar, FL, USA) worn around the hip. The devices will be worn during daytime for 7 consecutive days to assess a full weekly period. The sampling epoch will be set at 10 s [111]. Time per day spent in moderate physical activity (MPA; 1952–5723 counts per minute, > 3 MET) and vigorous physical activity (VPA; > 5274 counts per minute, > 6 MET) is determined based on the raw accelerometer counts and the ActiLife® computer software, with cut-off values derived from Freedson et al. [112]. Participants will fill in a non-wear time sheet (e.g. to assess physical activities during which it was not possible to wear the monitor, such as swimming). Physical activities listed on the non-wear time sheet will be included as moderate-to-vigorous physical activities, based on the intensity levels defined in the Physical Activity Compendium [113, 114]. To be included in the data analyses, participants will need at least 5 valid days, including ≥4 valid weekdays and ≥ 1 valid weekend day [115]. Following Herrmann et al. [116], only days with at least 10 h of wear time are considered a valid measure of daily physical activity. The validity of the Actigraph accelerometer device has been documented previously [117]. To the best of our knowledge, no minimal clinically important change (MCID) scores are currently available for physical activity in patients with MDD. The ACSM recommends that individuals should accumulate at least 150 min of moderate-to-vigorous physical activity per week [91]. This is in line with a study by Hoffman et al. [59] showing that in patients with MDD there is a linear increase associated with self-reported exercise regarding the probability of at least partial remission until 150 min of exercise per week, whereas the response curve flattens off beyond this threshold.

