### Data collection and statistical analysis

Types of data to be collected include: quantitative data on social and demographic background, anthropometric measurements, physical activity, cardiorespiratory fitness, exercise-related variables (cognitive and social determinants), indicators of psychological functioning, cardiovascular risk factors, and biomarkers of MDD; and qualitative data, based on semi-structured interviews, on the acceptability and perceived usefulness of the intervention among the patients. The collected data will be entered and merged into a single datafile. Statistical analysis will be performed using SPSS.

Treatment group, age, gender, baseline HAMD17 score, and the amount of previous depressive episodes will be selected as covariables. Changes in outcome variables over the three time points will be analysed using repeated-measures analyses of covariance (rANCOVAs), with a between-subject factor group (IG vs PCG) and a within-subject factor time (baseline, post intervention, follow-up). If significant group or time interactions are present, Bonferroni-adjusted post-hoc tests will be performed to identify individual differences. The statistical significance level will be defined at α = 0.05. Effect sizes will be calculated according to the recommendations of Cohen [183], with 0.49 ≥ *d* ≥ 0.20 indicating small effect (e.g. negligible practical importance), 0.79 ≥ *d* ≥ 0.50 indicating medium effect (moderate practical importance), and *d* ≥ 0.80 indicating large effect (crucial practical importance).

In the case of missing values (e.g. when patients drop out before follow-up), all analyses will be performed with and without intention to treat [184]. After a thorough dropout analysis, a decision will be reached regarding the method best suited to analyse intention-to-treat effects (e.g. last observation carried forward, imputation of missing values) [185].

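### The intention-to-treat method for the 12-month outcome is left open until dropout has been analysed, LOCF is a candidate, and the accelerometer wear rule as worded excludes randomised patients

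*Protocol article*

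**What the plan says.** All places are in the protocol article.

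- **Study design** lists "allocation concealment, single-blinding, and intention-to-treat analysis" among the trial's features, and the abstract repeats this.
- **Data collection and statistical analysis** says that, where values are missing, "all analyses will be performed with and without intention to treat". It then adds: "After a thorough dropout analysis, a decision will be reached regarding the method best suited to analyse intention-to-treat effects (e.g. last observation carried forward", with imputation of missing values as the second example. Neither run is called primary. The planned model is a repeated-measures ANCOVA over baseline, post and follow-up.
- **Objective physical activity** (the primary outcome) says: "To be included in the data analyses, participants will need at least 5 valid days", of which at least four must be weekdays and one a weekend day. It adds that "only days with at least 10 h of wear time are considered a valid measure of daily physical activity".
- **Abstract, Methods** gives the timing: "Data assessments will take place 2–3 weeks after admission to in-patient treatment (baseline), and 6 weeks (post) and 12 months (follow-up) after discharge". The primary outcome is activity at the last of these visits. The intervention section places the two face-to-face meetings "during the clinical treatment which lasts between 6 and 8 weeks on average", so the baseline week falls within the in-patient stay.
- **Recruitment and power calculations** assumes d = 0.30, one-tailed α 0.05 and power 0.80. It needs 278 evaluable patients and randomises 334 to allow for 20% dropout.

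**The concern.** Three features act on the same number, the 12-month group difference.

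First, the text does more than leave the ITT method unstated. It schedules the choice for after dropout has been examined, and it gives no safeguard that the people choosing will not know the arms. With two runs planned and neither primary, a reader of the results could not tell which one carries the claim.

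Second, LOCF suits this endpoint badly. The trial asks whether activity is maintained a year after discharge. The only earlier values come from the hospital stay and from 6 weeks after discharge. Carrying the first dilutes a real effect. Carrying the second credits dropouts with an early effect that may have faded. LOCF also treats the filled-in values as observed, so the standard errors do not reflect the missing information.

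Third, wear compliance is behaviour after randomisation and is plausibly related to activity itself. Excluding patients for poor wear departs from analysing everyone as randomised, and the sample size allows for dropouts only.

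**Working it through.** **Reproducing the plan's figure.** The two-sample t-test for d = 0.30, one-tailed α 0.05 and power 0.80 needs 138.07 per arm. That rounds up to 139, or 278 in total, which matches. The randomised number matches 278 × 1.2 = 333.6, i.e. 334. After 20% loss, 334 × 0.8 = 267 remain, with 79% one-tailed power.

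**What LOCF would estimate.** Inputs: 20% dropout and 12-month d = 0.30 from the power section. Assumptions: SD 1, equal dropout in both arms, dropout unrelated to outcome, no group difference at baseline. Let q be the share of dropouts who have a 6-week value, and d6 the 6-week effect:

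LOCF target = 0.8 × d12 + 0.2 × q × d6

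The documents give no d6 for this trial. The value 0.72 is the short-term effect in one cited trial of orthopaedic rehabilitation in-patients; 0.50 and 0.30 are shown for range.

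With d12 = 0.30:

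| q | d6 | LOCF target | Change |
|---|---|---|---|
| 0 | any | 0.8 × 0.30 = 0.24 | −20% |
| 0.5 | 0.30 | 0.24 + 0.03 = 0.27 | −10% |
| 0.5 | 0.50 | 0.24 + 0.05 = 0.29 | −3% |
| 0.5 | 0.72 | 0.24 + 0.072 = 0.312 | +4% |
| 1 | 0.30 | 0.24 + 0.06 = 0.30 | 0 |
| 1 | 0.50 | 0.24 + 0.10 = 0.34 | +13% |
| 1 | 0.72 | 0.24 + 0.144 = 0.384 | +28% |

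The bias is zero when 0.2 × q × d6 = 0.06. That is q = 0.06/0.144 = 42% for d6 = 0.72, and q = 0.06/0.10 = 60% for d6 = 0.50.

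**False positives if the 12-month effect is zero.** The target is then 0.2 × q × d6. The one-sided rejection rate with 167 per arm (normal approximation) is Φ(target × √(167/2) − 1.645), against a nominal 5%:

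| d6 | q = 1: target | q = 1: rejection | q = 0.5: target | q = 0.5: rejection |
|---|---|---|---|---|
| 0.30 | 0.06 | 13.6% | 0.03 | 8.5% |
| 0.50 | 0.10 | 23.2% | 0.05 | 11.7% |
| 0.72 | 0.144 | 37.1% | 0.072 | 16.2% |

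If every carried value is baseline (q = 0), the rate stays at 5%.

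**Invalid wear.** The documents give no invalid-week rate, so 5% and 10% are assumed.

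- Only the 12-month week must be valid: 334 × 0.8 × 0.95 = 254 and 334 × 0.8 × 0.90 = 240. One-tailed power is about 77% and 75%.
- A complete-case repeated-measures ANCOVA needs all three weeks, with independent losses: 334 × 0.8 × 0.95³ = 229 and 334 × 0.8 × 0.90³ = 195. One-tailed power is about 73% and 67%.

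The second pair describes complete-case analysis only. LOCF or imputation would fill the gaps, so these losses and the LOCF bias do not apply to one and the same analysis.

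**The case against.** The strongest reply is that the article condenses a fuller plan, and that the missing-data method is commonly settled in a statistical analysis plan. That disposes of any complaint about absent detail, such as a missing-not-at-random analysis. It does not dispose of this point, because the article itself states when the choice will be made and what the candidates are.

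Several stronger readings are tempting, and the documents do not support them:

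- *The method will be picked after unblinding, knowing its effect on the result.* The text ties the decision to a dropout analysis and does not say that outcomes by arm will have been seen. Researchers are not blinded to allocation while outcome assessors are, so the risk is real. What can be said is that no blinding of the choice is stated.
- *LOCF is the preferred method.* It is one of two examples, and multiple imputation would fall under the other.
- *The carried value is systematically wrong because effects are known to fade.* The statement "Although the group difference diminished until 12-month follow-up, the intervention group still reported increased physical activity levels" concerns a cited trial in orthopaedic in-patients. This trial plans telephone contacts every two weeks and message prompts up to month 12. For the one counselling trial in depressed out-patients, the power section gives a single odds ratio across 4, 8 and 12 months.
- *The wear rule flatly contradicts ITT.* It can be read as defining when a measurement is valid, so that an invalid week becomes a missing value. The missing-data paragraph gives dropout only as an example of missingness. The literal wording still makes inclusion in the analyses conditional on wear, so it needs correcting.

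**Conclusion.** The point holds in a limited form. The article defers the ITT method until dropout has been analysed, states no blinding to arm for that choice, keeps LOCF as a candidate and names no primary run.

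The possible LOCF distortion, from 0.24 to 0.384 around a true 0.30, marks two extremes and is not a forecast. The upper end needs every dropout to leave after the 6-week visit and an early effect borrowed from another population. Because the direction depends on when patients leave, LOCF cannot be defended as conservative. If there is an early effect and none at 12 months, carried 6-week values raise the false-positive rate above 5%.

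The wear rule as worded conflicts with the promised ITT analysis. Its cost in power is modest if only the 12-month week counts: 77–75%, against 79% after the planned dropout alone. The larger loss, to 73–67%, needs a complete-case analysis of all three waves and independent losses. All of these power figures rest on assumed invalid-week rates.

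**What to change.** Before any outcome data by arm are seen, amend the analysis section as follows:

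1. Name one primary ITT analysis of 12-month activity. It can be a likelihood-based mixed model on the available post and 12-month activity of all randomised patients, with baseline activity as covariate. Multiple imputation by arm is the alternative.
2. Delete LOCF.
3. State in the primary-outcome section that a week failing the wear rule is a missing value, handled by the primary method, and not a reason to exclude the patient.
4. Label the run without ITT (completers) as a sensitivity analysis.

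A delta-adjusted analysis for values missing not at random would be a useful addition but is optional.

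The cost is a change of wording and a little more analysis work. SPSS, already the planned software, can do either method. No visit, measurement or patient is affected.

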### Participants

#### Recruitment and power calculations

Clinical in-patients aged 18–65 years with a current diagnosis of major depression (ICD-10) will be continuously recruited from the Psychiatric Services Solothurn, Psychiatric Clinics of the University of Basel, Psychiatric Clinic Wyss, Münchenbuchsee, and the Psychiatric Clinic Sonnenhalde, Riehen. In previous studies with non-depressed individuals, individually tailored physical activity promotion was associated with a moderate effect (*d* = 0.50) on the primary outcome (physical activity) [80, 81]. So far, only one study exists examining physical activity counselling among out-patients with depression, yielding an adjusted odds ratios of 2.27 across the 4-month, 8-month, and 12-month follow-up (corresponding *d* = 0.45). Conversely, a relatively small effect size (*d* = 0.28) was observed in a Cochrane review of intervention studies promoting physical activity among generally healthy people [92]. Similarly, remote interventions such as telephone-based, app-based, and Internet-based coaching versus a control group were associated with rather small effect sizes for change in physical activity (*d* = 0.20) [93]. Given these observations, we assume a small-to-moderate effect of our intervention on the primary outcome (*d* = 0.30). Accordingly, the optimal sample size to detect a significant effect at follow-up is 278 participants (two independent groups, one-tailed, α-error probability = 0.05, power = 0.80). With 20% expected dropouts from baseline to follow-up [94], the targeted sample size is *N* = 334 (IG, *n* = 167: PCG, *n* = 167). This means that every centre will recruit approximately 40 participants per year (*n* = 20 in the IG, *n* = 20 in the PCG). Dependent on the size of the clinics, this corresponds to a recruitment rate of 20–25% of the patients. Enrolment will be systematically monitored by the sponsor-investigator in order to recruit a sufficient number of participants within the planned timeframe.

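### The missing-data method for the intention-to-treat result is to be chosen after the dropout analysis, with last observation carried forward as a candidate, so control of the 5% error rate is not guaranteed

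*Protocol article*

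**What the plan says.** All references are to the protocol article.

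- **Principle.** The abstract and the Study design section list, among the design features, "allocation concealment, single-blinding, and intention-to-treat analysis".
- **Primary time point.** In the abstract: "The primary outcome is objectively assessed physical activity at follow-up". Under Data assessment, baseline falls 2–3 weeks after admission, the post visit 6 weeks after discharge, and follow-up 12 months after discharge.
- **Missing values.** Under Data collection and statistical analysis, "all analyses will be performed with and without intention to treat" when values are missing. Then, after a dropout analysis, "a decision will be reached regarding the method best suited to analyse intention-to-treat effects (e.g. last observation carried forward, imputation of missing values".
- **Accelerometer data.** Under Objective physical activity: "To be included in the data analyses, participants will need at least 5 valid days".
- **Durability of the effect.** On a similar programme in orthopaedic in-patients, with a short-term effect of d = 0.72, the background says: "Although the group difference diminished until 12-month follow-up". The same sentence goes on to say that the intervention group still reported raised activity.
- **Blinding.** Under Study design, patients and outcome assessors are blinded. Clinicians, researchers and facilitators are not.

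**The concern.** This is more than a detail left for an analysis plan. The article states a sequence: look at the dropout, then pick the method. It sets no rule for picking and does not require the choice to be made before outcomes by arm are known. The researchers are not blinded to allocation, and the data monitoring section foresees an interim analysis coordinated by a committee that includes the sponsor-investigator and clinic researchers. With a fifth of patients expected to be lost, several analyses of the same 12-month outcome will exist, and the text does not say which one counts.

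LOCF adds a separate problem. For a patient lost before month 12, the value carried forward comes either from an in-patient week or from 6 weeks after discharge. The trial asks whether activity is maintained to 12 months. LOCF supplies that answer by assumption for everyone who left. If an early effect fades, LOCF counts part of it as a 12-month effect.

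**Working it through.** **The plan's own figures.** The sample size rests on the statement "we assume a small-to-moderate effect of our intervention on the primary outcome (*d* = 0.30") and on "two independent groups, one-tailed, α-error probability = 0.05, power = 0.80". A one-sided two-sample t-test with these inputs needs 139 per arm, 278 in total, as stated. The target is 278 × 1.20 = 334, or 167 per arm. These inputs are used below. The analysis section gives α = 0.05 without a side, so both are shown.

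**What LOCF estimates.** Let p be the dropout proportion, s the share of dropouts who have a 6-week value, and d6 and d12 the true standardised effects at 6 weeks and 12 months. Baseline values carried forward contribute no group difference on average. With equal SDs and random dropout,

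expected LOCF difference = (1 − p)·d12 + p·s·d6.

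If d12 = 0, the bias is p·s·d6. The bias can also go the other way: with p = 0.20, s = 0 and d12 = 0.30, LOCF gives 0.80 × 0.30 = 0.24.

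**Error rate of a single unadjusted 12-month test when d12 = 0.** SE = √(2/167) = 0.109 SD. One-sided error = 1 − Φ(1.645 − bias/SE). Two-sided error uses 1.960 and adds the lower tail. With p = 0.20:

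| d6 | Dropouts with a 6-week value | Bias (SD) | One-sided | Two-sided |
|---|---|---|---|---|
| 0.30 | half | 0.030 | 8.5% | 5.9% |
| 0.30 | all | 0.060 | 13.6% | 8.5% |
| 0.50 | half | 0.050 | 11.7% | 7.4% |
| 0.50 | all | 0.100 | 23.2% | 15.0% |
| 0.72 | half | 0.072 | 16.2% | 10.1% |
| 0.72 | all | 0.144 | 37.1% | 26.0% |

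Simulation with a baseline-adjusted 12-month ANCOVA agrees for d6 = 0.50:

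- Assumed correlations 0.4, 0.4 and 0.6: 12% one-sided and 8% two-sided (half), up to 25% and 16–17% (all).
- All correlations 0.5: 14.5% and 8.8% (half), up to 29.0% and 18.7% (all).

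In the same runs completers and multiple imputation stayed near 5%. That follows from the random dropout built into the simulation.

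**Closer to the planned test.** The article specifies a repeated-measures ANCOVA over three visits with Bonferroni-adjusted post-hoc tests. Assuming three comparisons, the two-sided level per comparison is 0.05/3 = 1.67%, with critical value 2.394. For d6 = 0.50 the formula gives 2.9% (half) and 7.0% (all), and simulation gives 3.2% and 7.9%. For d6 = 0.72 simulation gives 5.3% and 15.9%. The absolute figures are lower, yet 3.2% and 7.9% are still about 1.9 and 4.7 times the 1.67% level. The requirement of a significant interaction before post-hoc testing is not modelled.

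**Choice among methods when there is no effect at any time.** Simulation used correlations 0.3–0.7. Each of completers, LOCF and multiple imputation, fixed in advance, has a one-sided error of 4.4–5.6%. If the best of the three may be reported, it is 6.4–7.1% at 20% dropout and 7.3–8.0% at an assumed 30%.

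**The case against.** The strongest reply is that the choice is tied to a dropout analysis, not to results. A choice made from dropout patterns alone, blind to arm and outcome, need not inflate the error at all. This stands, and it is why the conclusion is that control is not guaranteed. A reader might infer that the 5% rate is actually broken. The article does not show that, and it nowhere says that the most favourable of several results will be reported.

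A reader might also infer that no analysis is primary. That goes too far, because intention to treat is named twice as the design. What is open is how it handles missing data and which result prevails if the two versions disagree.

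The evidence for fading is limited. The orthopaedic programme's group difference shrank, but activity in its intervention group was still raised, so a 12-month effect of exactly zero is an assumption. The background's small, non-significant follow-up effect concerns depression, not activity. The one counselling trial in patients with MDD reported higher activity at follow-up, with an odds ratio of 2.27 across 4, 8 and 12 months. Counselling here continues to month 12, and nothing in the article says that its effect peaks at 6 weeks.

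The wear-time rule could be read as removing randomised patients from the trial analysis. It is primarily a validity rule for accelerometer weeks, and the article does not say that invalid weeks bypass the missing-value provisions. It needs one clarifying sentence.

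Finally, LOCF is only an example, and the other example, imputation, is acceptable. That is true. But a stated plan to choose later is not cured by one acceptable candidate on the list.

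**Conclusion.** The point holds in a limited form. The article announces intention to treat, then leaves its missing-data method to a decision after the dropout analysis, without a blinding condition, with LOCF on the list and without saying which version decides. Control of the 5% error rate is therefore not guaranteed.

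Free choice among methods costs little on its own: about 6–8% in place of 5%, and only if the best result is reported. LOCF could cost more: about 12–25% one-sided or 7–17% two-sided for d = 0.5 at 6 weeks, reaching 29% and 19% if all correlations are 0.5, and less under Bonferroni adjustment. These LOCF figures assume a 12-month effect of zero, random dropout of 20% equal in both arms, and half to all dropouts having a 6-week value. None of these except the 20% is in the article. They illustrate the risk and do not predict this trial's error rate. Severity: should-fix.

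**What to change.** Replace the missing-data provisions in the analysis section with a rule fixed before any outcome data by arm are seen, including at the interim analysis:

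- One primary intention-to-treat analysis of all randomised patients in their assigned arm, by either a likelihood-based mixed model on all available visits or multiple imputation using baseline and 6-week values.
- LOCF removed as a candidate.
- An invalid wear week counted as a missing value, not as exclusion of the patient.
- The completers analysis and a missing-not-at-random analysis as sensitivity analyses only. The latter matters because the primary method assumes that missingness is explained by observed data, and only the intervention arm is telephoned through to month 12, so dropout may differ by arm.
- The dropout analysis descriptive, with no role in selecting the primary method.

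The cost is a few sentences. The named software can fit the model, and no extra patients or visits are needed.
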